### Data analysis

Data will be stored and analysed with SPSS-12.0 After checks for missing values and for normality of the data, regression techniques will be applied by a blinded analyst using the 'intention-to-treat' principle. Primary and secondary outcome measures will be reported for the in-hospital and home situations, and for 6-week and 3-month follow-up.

The primary research question will be tested using Student's t-tests with a p-value of 0.05 being regarded as significant.

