**Discussion:**

Because restricted knee ROM affects functional activities, knee ROM and knee function are regarded as the primary indicators of successful TKA. Potential effects of the intervention under study include rapid return of knee flexion accompanied by earlier return to functional activities of daily life. If patients benefit significantly from prolonged CPM use, this treatment should be added to the standard PT treatment at home.

We expect the additional home CPM programme to be more effective than the usual physiotherapy programme, resulting in a difference in ROM of at least 5°, 17 days after surgery. This clinically important difference, with a possible flexion ROM of about 100°, is expected to lead to better functioning in activities of daily life, like walking, and earlier ability to cycle. These advantages should result in earlier and increasing independence.

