### Research question

What is the effect on range of motion and functional status of prolonged use of a continuous passive motion device at home in addition to physical therapy, compared to physical therapy alone, in patients with limited flexion range of motion (less than 80°) of the knee at discharge from the hospital following total knee arthroplasty?

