### Interventions

During the in-hospital period, all patients will receive a standardised PT programme, involving 20 minutes of PT per day for four days. During the first two weeks after discharge, patients in the experimental group will receive CPM for 4 hours a day in addition to regular PT treatment. Patients in the control group will receive only regular PT treatment (usual care).

From day 18 onward, all patients will receive regular PT treatment until 3 months after surgery, if indicated.

The post-clinical PT will be standardised in terms of treatment objectives. All patients will receive treatment consisting of active and passive mobilisation of the knee joint, active strengthening of the m. quadriceps, and training of ADL functions (gait, sit to stand and stair climbing).

Outcome assessment

After baseline variables have been collected, outcome measures will be assessed at 17 days, 6 weeks and 3 months after surgery, during normal routine assessments at the orthopaedic clinic (table 1). The outcome assessor will be blinded.

Primary outcome measures are:

1. functional status, using the WOMAC function score [7,8] and the Knee Society Score[9]; and

2. range of motion, assessed with a long-arm goniometer [10].

Secondary outcome measures are:

a. perceived effect, using a 7-point Likert scale;

b. postoperative medication use (amount; type will be standardised);

c. satisfaction with treatment, on an 11-point Likert scale;

d. satisfaction with treatment result, on an 11-point Likert scale;

e. adherence to treatment protocols and use of CPM (in hours), measured with a patient diary;

f. quantity, duration and nature of PT intervention.

The study design is depicted in figure 1

The first primary endpoint of the study is on day 17 after surgery, which is when the experimental treatment stops and short-term effects are measured.

The second endpoint is at 3 months after surgery.

Table 1 shows the timing of the outcome assessment

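### Three measures are called primary and two endpoints are named, all under an unadjusted 0.05 with no ordering or success rule, while only knee flexion at the end of CPM has a sample size

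*Protocol article*

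**What the plan says.** All references are to the protocol article.

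- **Primary measures** (Outcome assessment, under Interventions). The first item is "functional status, using the WOMAC function score [7,8] and the Knee Society Score[9]; and"; the second is range of motion by goniometer. That makes three unranked measures.
- **Time points** (same place). "The first primary endpoint of the study is on day 17 after surgery", and then: "The second endpoint is at 3 months after surgery". The word primary is attached only to day 17. Six weeks is also assessed but is not named as an endpoint.
- **Research question.** It covers both domains: "What is the effect on range of motion and functional status of prolonged use of a continuous passive motion device at home".
- **Test** (Data analysis). "The primary research question will be tested using Student's t-tests with a p-value of 0.05 being regarded as significant". Sidedness is not given.
- **Sample size** (Power analyses). It rests on one outcome only: a 5° difference in knee flexion, SD 8°, when CPM stops, with alpha 0.05, power 80% and 28 per group. The planned total is 70.
- **Objective.** The primary purpose is stated as long-term benefit of continuing CPM after discharge.
- **Use of the result** (abstract, Discussion). "If patients benefit significantly from prolonged CPM use, this treatment should be added to the standard PT treatment at home".

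**The concern.** The article uses one threshold, 0.05, for a primary question that covers several outcomes, and it does not say which of them decides the answer. If range of motion is significant and function is not, or day 17 is significant and 3 months is not, the article offers no agreed reading. Yet a significant benefit is to lead to adding home CPM to standard treatment, and the Dissemination section carries that to guidelines and insurers.

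Three places also point in different directions. The sample size and the abstract's expected 5° point to flexion at day 17. The outcome list gives function equal standing. The Objective points to the long term. Without a rule, the outcome that decides the trial can be chosen after the results are seen, and the 5% error rate implied by the threshold would not hold.

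**Working it through.** **Inputs from the article:** three primary measures; day 17, and possibly 3 months; 0.05 per test; 5°, SD 8°, 80% power, 28 per group; 70 patients at 1:1, so 35 per group.

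**Assumptions:** two-sided tests; each measure is one test per time point; any single significant result counts as success; a common correlation ρ between test statistics, which the article does not give, so a range is shown.

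**Step 1. The plan's own figure.** n per group = 2(1.960 + 0.842)² × SD²/Δ² = 2 × 7.849 × 64/25 = 40.2, so 41, not 28. With Δ = 6° the same formula gives 2 × 7.849 × 64/36 = 27.9, so 28. This discrepancy is a separate matter. It is noted because the power figures in step 4 use 5° and SD 8° as stated.

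**Step 2. Independent tests (ρ = 0).**

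- Either direction: 1 − 0.95³ = 14.3%; 1 − 0.95⁶ = 26.5%.
- Favouring CPM: 1 − 0.975³ = 7.3%; 1 − 0.975⁶ = 14.1%.

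**Step 3. Correlated tests.** With c = 1.96 and k tests of common correlation ρ:

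- Either direction: 1 − ∫ φ(u) [Φ((c − √ρ·u)/√(1−ρ)) − Φ((−c − √ρ·u)/√(1−ρ))]^k du
- Favouring CPM: 1 − ∫ φ(u) Φ((c − √ρ·u)/√(1−ρ))^k du

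| ρ | 3 tests, either direction | 3 tests, favouring CPM | 6 tests, either direction | 6 tests, favouring CPM |
|---|---|---|---|---|
| 0 | 14.3% | 7.3% | 26.5% | 14.1% |
| 0.5 | 12.5% | 6.3% | 20.7% | 10.4% |
| 0.7 | 10.9% | 5.5% | 16.4% | 8.2% |
| 0.9 | 8.4% | 4.2% | 10.8% | 5.4% |
| One test | 5% | 2.5% | 5% | 2.5% |

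Simulation with t-tests at 35 per group agrees: for six tests in either direction, 26.2% at ρ = 0, 20.7% at 0.5 and 16.5% at 0.7.

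**Step 4. Cost of the possible remedies, for flexion at 35 per group.** The noncentrality is (5/8) × √(35/2) = 2.61 on 68 degrees of freedom.

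- Single primary outcome at 0.05: power 73%.
- Bonferroni over six (0.05/6 = 0.0083): power 46%.

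A single primary outcome, or a fixed order with flexion first, keeps the 73%.

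**The case against.** Four points can be made for the plan.

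**Nothing says that one success is enough.** The research question joins range of motion and functional status, and requiring success on both is open on that wording. Under an all-must-succeed rule the error rate would not exceed the nominal level. This stands: the inflation is conditional on the any-one-suffices reading, which the article neither states nor excludes.

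**Three months is not called primary.** A reader might infer six primary tests, because a first primary endpoint suggests another and the Objective stresses the long term. The inference is fair, but the article does not say it. The three-test figures therefore have to be given beside the six-test ones. They are still more than double the nominal level for correlations up to 0.7.

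**The larger range is easily misread.** A reader might take 16–26% as the chance of wrongly concluding that CPM works. With two-sided tests that range also counts false results against CPM; the chance in its favour is 8–14%, against 2.5%. One-sided tests at 0.05 would give about 15–26% in favour of CPM, against 5%, but the article does not say that its tests are one-sided. The lower ends rest on an assumed correlation of 0.7 and fall further if it is higher.

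**A condensed article may leave multiplicity to a fuller document.** True, and the absence of an adjustment procedure alone would not be a finding. What remains is what the article does fix: several unranked primary measures, a second endpoint of unclear standing, one unadjusted threshold, and a sample size for only one of the outcomes.

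**Conclusion.** The concern holds in this form. The article does not identify which result answers its primary question, and its stated threshold does not secure a 5% error rate across the outcomes that it calls primary.

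If any one significant result counts, the excess is moderate if only day 17 is primary (11–14% in either direction) and large if 3 months is primary too (16–26%, or about 11% at a correlation of 0.9). The rates favouring CPM are about half of these, with a nominal level of 2.5%. The figures rest on two-sided tests and assumed common correlations.

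The documents do not support a flat statement that the trial runs six primary tests, or that its chance of falsely declaring CPM effective is 16–26%. The lack of a decision rule does not depend on any of these figures, and it should be settled before the analysis.

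**What to change.** State in Outcome assessment and Data analysis that knee flexion by goniometer at day 17, the outcome in the power calculation, is the single primary outcome, tested at two-sided 0.05. Make WOMAC function, the Knee Society Score and all 3-month outcomes secondary. Either report them with 95% confidence intervals, or test them in a pre-stated order, each at 0.05 only while every earlier test has succeeded.

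Reconcile this with the Objective. One way is to place flexion at 3 months directly after flexion at day 17, so that a non-significant function score cannot block the long-term test. If the sponsor prefers co-primary outcomes or 3 months first, that also settles the point once the rule is written down, but the article gives no sample size for those outcomes.

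**Cost:** a wording change before analysis. Function and the 3-month results lose unconditional primary status, which matters because the research question names function and the Objective names the long term. Flexion keeps about 73% power at 35 per group, against 46% under Bonferroni over six.

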### Participants

We intend to include 70 patients in the study, who must be eligible for unilateral primary TKA as a result of osteoarthritis of the knee. Patients will be included if they have less than 80° of flexion range of motion 4 days after surgery, are able to understand and speak Dutch, are not suffering from mental disabilities and are resident inside the 'Maastricht heuvelland' region. Patients will be excluded if they need to stay in hospital for more than 5 days after surgery or show relevant co-morbidity influencing mobility (e.g. claudication, other prosthesis) or are operated upon using minimally invasive surgery.

Eligible patients will be contacted one week before planned surgery, and will be randomised into two groups after signing an informed consent form, on the day they are discharged from hospital. Patients will thus have 10 days in which to consider participation.

Blocked and concealed randomisation with a block size of 4 will ensure equal distribution of patients over the two treatment groups. Groups will be prestratified on preoperative flexion mobility of the knee.

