### Power analyses

We assume a difference of more than 5° of knee flexion mobility (SD 8°) at the end of the CPM application to be clinically relevant. With an alpha of 0.05, and a power of 80%, we will need 28 patients per group to prove this.

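### Naming a covariate-adjusted model, rather than an unadjusted t-test, as the primary analysis would be a free gain in precision if baseline flexion is prognostic

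*Protocol article*

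**What the plan says.** Data analysis section, on the primary test: "The primary research question will be tested using Student's t-tests", at a significance level of 0.05. No covariate or stratum is attached to it. The preceding lines of that section say that "regression techniques will be applied by a blinded analyst using the 'intention-to-treat' principle", with no model, no covariates and no statement of which question the regression answers.

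Participants section, on the design: "Groups will be prestratified on preoperative flexion mobility of the knee". Allocation is in blocks of 4. The number of strata and their cut-points are not given. On eligibility: "Patients will be included if they have less than 80° of flexion range of motion 4 days after surgery". Patients are randomised on the day of discharge, so both flexion measurements belong to the period before treatment allocation and are legitimate covariates.

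Power analyses section: "We assume a difference of more than 5° of knee flexion mobility (SD 8°) at the end of the CPM application to be clinically relevant". It gives 28 patients per group; the planned total is 70, or 35 per group.

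**The concern.** Stratified randomisation balances the arms on preoperative flexion. If that variable predicts day-17 flexion, balance makes the estimated treatment difference less variable from trial to trial. A two-sample t-test does not use this: it leaves the variation due to preoperative flexion in its error term. Its standard error then exceeds the true sampling standard deviation, its confidence interval is too wide, and it rejects less often than it should.

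Day-4 flexion is not a stratification factor, so chance imbalance between the arms is possible, and the t-test does not correct for it.

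At stake is power and precision in a trial of 70 patients, not protection against a false positive. There is also a smaller point of clarity: two kinds of analysis are named and only one is linked to the primary question.

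**Working it through.** **Inputs from the document.** Difference 5°, SD 8°, alpha 0.05, power 80%, 28 per group (Power analyses); 70 patients, blocks of 4, stratification on preoperative flexion (Participants).

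**Assumed, because not given.** The correlation r between preoperative and day-17 flexion (0 to 0.5 shown); two strata split at the median of preoperative flexion; normal data; two-sided testing; all 70 patients analysed.

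**1. The plan's own figure.** n per group = 2(1.960 + 0.842)² × 8²/5² = 40.2, so 41 two-sided. One-sided it is 2(1.645 + 0.842)² × 8²/5² = 31.7, so 32. The stated 28 is not reproduced. That is a separate matter. It enters here only because the t-test at 35 per group then has about 73% two-sided power (noncentral t).

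**2. Standard errors at 35 per group.** Unadjusted: 8 × √(2/35) = 1.91°. Adjusted for a covariate with correlation r, the residual SD is 8√(1−r²):
- r=0.3: 7.63 × √(2/35) = 1.82°
- r=0.5: 6.93 × √(2/35) = 1.66°

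**3. How conservative the t-test is.** A median split captures a share 2/π = 0.637 of the variance of a normal covariate. With strata balanced, the true SD of the estimate is about 1.912 × √(1 − 0.637r²), and the true size is about 2(1 − Φ(1.96/√(1 − 0.637r²))):
- r=0.3: SD 1.86, size about 4.4%
- r=0.5: SD 1.75, size about 3.3%

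**4. Simulation with the stated blocks of 4** (70 patients, two strata, 6,000 runs per setting; preoperative flexion is the only covariate in the ANCOVA):

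| r | t-test mean SE v true SD (no effect) | t-test size | t-test power | ANCOVA power |
|---|---|---|---|---|
| 0 | 1.90 v 1.92 | 5.1% | 73% | 73% |
| 0.3 | 1.90 v 1.86 | 4.6% | 73% | 76% |
| 0.5 | 1.91 v 1.76 | 3.4% | 75% | 84% |

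The simulated sizes agree with step 3 within simulation error (about 0.3 percentage points). ANCOVA held its size at 5.0% to 5.3% throughout.

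**5. Cross-check of power at r=0.5.** The t-test rejects when the estimate exceeds about 1.996 × 1.912 = 3.82°, so power is Φ((5 − 3.82)/1.754) = 75%. For ANCOVA, Φ(5/1.656 − 1.996) = 85%. Both are close to the simulation.

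**6. Day-4 flexion.** The Background section says about 50% of patients are below 80° on day 4. If day-4 flexion is normal, cutting at the median leaves 1 − 2/π = 36% of its variance. A correlation of 0.5 in all such patients becomes 0.5 × 0.603/√(0.75 + 0.25 × 0.363) = 0.33 in those enrolled, and 0.3 becomes about 0.19. Gains from this covariate may therefore be small. The calculation does not carry over directly to preoperative flexion.

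**The case against.** The strongest reply is that nothing here is invalid. An unadjusted t-test after stratified randomisation is unbiased and does not inflate type I error. That stands in full, and it limits the point to efficiency.

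Second, the prognostic value of preoperative flexion is never stated. A reader might infer from the stratification that the investigators expect it to be prognostic, and so that the standard errors are certainly too wide. The Participants section gives no reason for stratifying, and no correlation appears anywhere. The claim must stay conditional.

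Third, larger figures are tempting. With perfect balance on a covariate with r=0.5, the t-test's size would be 2(1 − Φ(1.96/√0.75)) = 2.4%. But blocks of 4 within strata do not balance a continuous variable perfectly, and two strata give 3.4%. Likewise, comparing adjusted power of 85% at r=0.5 with a fixed 73% suggests a 12-point gain. Stratification helps the t-test a little too, so the fair comparison is 75% v 84%, about 9 points.

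Fourth, the regression sentence may mean that an adjusted analysis is intended, and covariates may be left to a full protocol or analysis plan that is not shown. That is possible, but the sentence assigning a test to the primary question names t-tests. The t-tests might also be meant for change scores, which the article does not say. With equal SDs at both times, a change score has SD 8√(2(1−r)): 9.5° at r=0.3 and 8.0° at r=0.5. Up to r=0.5 it would be no more precise than the day-17 value alone.

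**Conclusion.** The point holds as an efficiency recommendation. The named primary test uses neither the stratification factor nor entry flexion as a covariate, and the regression sentence is not connected to it. If preoperative flexion is prognostic, the t-test is conservative and gives away power: about 3 points at r=0.3 and 9 points at r=0.5, at 35 per group for 5° and SD 8°. If it is not prognostic, adjustment costs nothing meaningful.

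The direction is secure given a prognostic covariate. The size is not, because r, the number of strata and the cut-points are assumptions, and the entry cut at 80° may weaken the contribution of day-4 flexion. The document does not support saying that the planned test is wrong or that its intervals are certain to be too wide. This is a free improvement.

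**What to change.** In the Data analysis section, replace the t-test sentence with wording such as: the primary comparison is the treatment effect on day-17 knee flexion from a linear regression with treatment, preoperative flexion (the stratification variable, entered as a continuous covariate) and day-4 flexion; an unadjusted t-test is reported as a sensitivity analysis. This also reconciles the two sentences, because the regression techniques then have a stated model and purpose.

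For WOMAC function and the Knee Society Score, use the same model with preoperative flexion, adding each score's own baseline value where it is collected. The article refers only to unnamed baseline variables and its Table 1 is not shown, so baseline collection of these two scores should be confirmed first.

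The cost is a sentence or two of text and two degrees of freedom. The flexion covariates are already required by the stratification and the eligibility check, and linear regression is standard in the stated software. The change should be made before outcome data are seen by arm.

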**Methods:**

In a randomised controlled trial we intend to investigate the efficacy of prolonged use of a continuous passive motion (CPM) device in the home situation as an adjunct to standardised physical therapy. The experimental treatment is compared to standardised physical therapy, in patients with osteoarthritis of the knee undergoing Total Knee Arthroplasty (TKA). Efficacy will be assessed in terms of faster improvements in range of motion and functional recovery.

Seventy patients with knee osteoarthritis undergoing TKA and experiencing early postoperative flexion impairment (less than 80° of knee flexion at the time of discharge) will be randomised over two treatment groups, a usual care group and an experimental group

The experimental group will receive CPM + physiotherapy for 17 consecutive days after surgery, whereas the usual care group will receive the same treatment during the in-hospital phase (i.e. about four days), followed by physical therapy alone (usual care) in the first two weeks after hospital discharge.

From 18 days to three months after discharge, both groups will receive standardised PT. The primary focus of rehabilitation will be functional recovery (e.g. ambulation) and regaining range of motion (ROM) in the knee.

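### The primary question is assigned to unadjusted t-tests alongside unspecified regression; one baseline- and stratum-adjusted repeated-measures model should be named as confirmatory

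*Protocol article*

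**What the plan says.** All references are to the protocol article.

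- **Data analysis**: after checks for missing values and normality, a blinded analyst applies regression techniques "using the 'intention-to-treat' principle". The section then states: "The primary research question will be tested using Student's t-tests with a p-value of 0.05 being regarded as significant". The regression sentence is not limited to secondary outcomes, and nothing links the two methods.
- **Interventions, outcome assessment**: "outcome measures will be assessed at 17 days, 6 weeks and 3 months after surgery". Day 17 is the first primary endpoint and 3 months the second. Range of motion, the WOMAC function score and the Knee Society Score are all primary measures.
- **Participants**: 70 patients, randomised in blocks of four and stratified on preoperative knee flexion. Entry requires flexion below 80° four days after surgery, so a flexion value around discharge exists for every randomised patient.
- **Power analyses**: the sample size is built on a day-17 difference of over 5° with an SD of 8°. The section concludes: "With an alpha of 0.05, and a power of 80%, we will need 28 patients per group to prove this".
- **Abstract, Methods**: "Efficacy will be assessed in terms of faster improvements in range of motion and functional recovery". The abstract's Discussion gives the expectation as "resulting in a difference in ROM of at least 5°, 17 days after surgery".

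**The concern.** Two methods are named in one short section without an order between them. If their results differ, the text does not settle which one decides the trial. The natural reading is that the t-test does, and it is the weaker of the two.

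A two-sample t-test takes one value per patient. It uses neither flexion at discharge nor the stratum that the randomisation was built on, although both are known before treatment diverges. It also makes no use of the other visits. At day 17 this costs precision in a small trial. At 3 months, if the test is run only on patients seen then, a patient with a day-17 value but no 3-month value contributes nothing. If slow recoverers are likelier to be lost and the treatment works, more control patients go missing, the remaining controls look better than they should, and the later effect is understated.

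**Working it through.** **1. The plan's own figure.** Inputs from Power analyses: difference 5°, SD 8°, alpha 0.05, power 80%. Sidedness is not stated; two-sided is assumed.

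n per group = 2 × SD² × (1.960 + 0.842)² / difference² = 2 × 64 × 7.849 / 25 = 40.2, so 41 (42 with the t distribution). One-sided gives 32 (33 with t). The stated 28 is not reproduced; it does follow from a 6° difference (27.9). That is a separate matter, but it means that the stated inputs leave little power to spare.

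**2. Day 17, unadjusted against baseline-adjusted.** 35 per arm (70/2), no loss, two-sided 0.05, noncentral t with 68 degrees of freedom. Adjustment for a baseline with correlation ρ reduces the SD to 8 × √(1 − ρ²). The values of ρ are assumed. The standard error is SD × √(2/35) = SD × 0.239.

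| Analysis | SD | Standard error | 5° / standard error | Power |
|---|---|---|---|---|
| t-test | 8.00 | 1.91 | 2.61 | 73.2% |
| Adjusted, ρ = 0.3 | 7.63 | 1.82 | 2.74 | 77.1% |
| Adjusted, ρ = 0.5 | 6.93 | 1.66 | 3.02 | 84.5% |

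Entry is restricted to flexion below 80°, which narrows the baseline range and may lower ρ.

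**3. Day 17, what the other visits add.** With a share d missing at day 17 and correlation ρ with the other visits, the effective number per arm is about 35(1 − d) / (1 − dρ²). Normal approximation, ρ from 0.3 to 0.7, all assumed:

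- d = 10%: 69.9% for the t-test on observed values, 70.3% to 72.0% for the likelihood model.
- d = 20%: 64.7% against 65.5% to 69.2%.

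The gain is 0.4 to 4.5 percentage points. At ρ of 0.5 or more, baseline adjustment gives more than this.

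**4. Three months, possible bias.** Simulation with 35 per arm and SD 8° at each visit. Everything else is assumed: true differences of 5° at day 17 and 3° at 3 months, correlation 0.4 to 0.8 between those visits, and loss after day 17 with odds rising 2.7- to 4.5-fold per 8° lower day-17 flexion. The t-test on observed 3-month values was compared with a likelihood estimate that also uses day-17 flexion.

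| Overall loss | Bias, observed-value t-test | Bias, likelihood estimate |
|---|---|---|
| 10% | about −0.1° to −0.5° | within 0.1° |
| 22% | about −0.2° to −0.7° | within 0.1° |
| Either, unrelated to flexion | none | none |

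The mechanism shows in a middle case (22% loss, 2.7-fold odds, correlation 0.6): about 26% of controls and 17% of the experimental arm are lost, and the bias is −0.36°. The largest bias needs the steepest gradient and the highest correlation together; repeat runs put that corner at 0.7° to 0.8°. The sampling SD of the 3-month estimate is about 2.1°.

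**The case against.** Much can be said for the plan as written, and three stronger readings that a reader might infer are not supported.

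- **That the t-test contradicts intention-to-treat.** The article states no complete-case rule and no per-visit rule. A t-test can be run on imputed values or change scores, and the intention-to-treat wording is attached to the regression techniques. Missing-data detail may sit in a fuller document that is not shown, so its absence here is no fault.
- **That 20% loss is expected.** No dropout rate is given. The gap between 70 recruited and 56 needed (2 × 28) is 14 patients, an enrolment margin and not a forecast. Assessments fall at routine clinic visits within three months, in patients from the region.
- **That the aim of faster improvement requires an arm-by-visit test.** The abstract's Discussion and the Power analyses make that aim a difference at day 17. A comparison at that fixed visit answers it. In the scenario above, an interaction would mostly describe the effect fading after day 17.

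It is also fair that the 3-month bias is modest, roughly 0.1 to 0.4 of a standard error, and depends wholly on assumed dropout, and that the repeated-measures part adds little at day 17. All of this stands. It does not answer the remaining point: the test that the article does fix ignores information already collected, and its relation to the regression is left open.

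**Conclusion.** The concern holds as an improvement to the stated analysis, not as an internal contradiction. The article names two methods without saying which is confirmatory, and the one tied to the primary question is unadjusted.

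The firmest gain is at day 17, from baseline adjustment: about 73% power rises to about 77% to 85%. This rests on 5°, SD 8°, 35 per arm, a two-sided 5% level and an assumed correlation of 0.3 to 0.5. The second gain is at 3 months and is conditional: it avoids an understatement of about 0.1° to 0.7° on an assumed 3° effect, and only if the t-test would use observed values and loss depends on earlier flexion. The point merits a change because that change is cheap, not because the planned test would be invalid.

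**What to change.** Replace the two sentences on regression and t-tests with one named confirmatory analysis:

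- a linear mixed model for repeated measures of flexion at day 17, 6 weeks and 3 months;
- terms for arm, visit, arm-by-visit, discharge flexion and preoperative-flexion stratum, with unstructured covariance;
- all randomised patients with at least one post-discharge value, analysed as randomised;
- the day-17 contrast as the primary test and the 3-month contrast as the second. The arm-by-visit term is there to give these contrasts and is not itself the test of faster recovery.

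Use the same form for the WOMAC function score and the Knee Society Score, each adjusted for its own baseline where collected. State whether the test is two-sided. If t-tests are kept, label them as supportive.

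Cost: analysis wording and slightly more programming, with no new data, visits or patients. The downside is reliance on data being missing at random, so add a short sensitivity analysis that lets unobserved values be worse than the model predicts.
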